##### Withdrawal of individual subjects

Patients can leave the study at any time for any reason if they wish to do so without consequences for their AE care. Investigators can decide to withdraw a patient from the study for urgent medical reasons. Reasons for withdrawal will be documented by the investigators. Withdrawal of participants has been accounted for in the sample size calculation.

If a participant prematurely discontinues study treatment, the patient will be encouraged to stay in the study to allow data collection at all remaining scheduled visits until completion of the planned end-of-study visit. The treating physician or research coordinator should aim to document the date of premature discontinuation from study treatment and the agreement of teh patient with collecting data and completing the remaining scheduled visits. Patients who fail the allocated therapy will, based on shared decision-making, continue with OTT or get screened and if eligible start with systemic immunomodulating therapy. During the follow-up period, patients will be monitored for effectiveness, safety, and satisfaction with the care received and have clinical assessments per schedule.

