### Informed consent

Subjects will be recruited from the patient population of each participating center. Possible eligible patients will be informed verbally about the study by a trained investigator. This may be in person or via telephone/video call. The patient will receive the participant information sheet and informed consent form (ICF) digitally or in print. Patients who agree to participate will be asked for written informed consent after reviewing the abovementioned information during a reflection period of at least one hour. In order to schedule the screening activities, it is allowed that the patient gives oral consent. The oral consent must be documented in the digital patient file. At the appointment of the screening activities the patient and the investigator will sign the informed consent form together. Allocated therapy cannot start before both parties have signed the ICF.

On the consent form, participants will be asked if they agree to the usage of their data should they choose to withdraw from the trial. Participants will also be asked for permission for the research team to share data to investigators, auditors, or regulatory authorities, where relevant. No ancillary studies are planned. This trial does not involve collecting biological specimens for storage.

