##### Rescue medication

For patients in the NB-UVB + OTT group, if sunburn occurs during NB-UVB, rescue medication consists of a one-time topical application of a class IV corticosteroid. For all patients, in case of severe uncontrolled AE during the study that requires rescue medication, a short course of oral prednisone can be prescribed [21]. Dosage and duration of this course will be determined by the treating physician. At the investigators’ discretion, rescue medication is allowed in other situations after consulting with the coordinating investigator.

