#### Sample size

The required sample size is determined for the primary endpoint EASI50 at 3 months follow-up. Based on previous research published in the literature incidences of 50% effectiveness for reaching EASI50 using NB-UVB, and of 20–30% using only OTT are to be expected [37–40].

Sample sizes of 134 in both arms achieve 90% power to detect a difference between the group proportions of 20 percentage points. The proportion in the NB-UVB + OTT treatment group is assumed to be 30% under the null hypothesis and 50% under the alternative hypothesis. The assumed proportion in the control group treated with OTT alone is 30%. The test statistic used is the two-sided *Z*-test pooled variance. The significance level of the test is 5%. Interim analyses for early stopping will not be conducted; hence, no correction of the significance level for interim analyses is required. Allowing for a drop-out rate of up to 15%, a total of 316 patients will be recruited.

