##### Follow-up of AEoSIs and SAEs

All AEoSIs and SAEs will be followed until they have abated, or until a stable situation has been reached. Depending on the event, follow-up may require additional tests or medical procedures as indicated, and/or referral to the general physician or a medical specialist. SAEs will be reported according to GCP guidelines until the study ends for the patient (when all 6 visits are completed, when the patient discontinues prematurely, or when the study is prematurely terminated).

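### Investigators may withdraw a patient from the study, not only from treatment, for urgent medical reasons, and the retention rule does not cover these patients

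*Protocol article*

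**What the plan says.** The section on withdrawal of individual subjects (protocol article) sets out three routes.

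- Patients may leave at any time and for any reason.
- Investigators have their own power: "Investigators can decide to withdraw a patient from the study for urgent medical reasons".
- Stopping treatment is handled separately: "If a participant prematurely discontinues study treatment, the patient will be encouraged to stay in the study", with data collected at the remaining scheduled visits up to the planned end-of-study visit. Patients who fail their allocated therapy also keep their scheduled assessments.

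On safety, the section on follow-up of AEoSIs and SAEs says that "SAEs will be reported according to GCP guidelines until the study ends for the patient". One of the end points it lists is "when the patient discontinues prematurely". For events already recorded, "All AEoSIs and SAEs will be followed until they have abated, or until a stable situation has been reached".

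The participant timeline sends patients who discontinue prematurely back to standard eczema care, together with those who have completed the trial. It also provides extra visits when therapy is switched or stopped, and a blinded assessor examines the patient at every visit.

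The primary outcome is EASI50 at 3 months, analysed by intention to treat. The objectives include long-term effectiveness and safety.

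**The concern.** The section separates stopping treatment from leaving the study and attaches retention only to the first. An urgent medical reason can require that NB-UVB or a topical drug be stopped. It does not by itself require that measurement stop. As worded, the investigator's power ends both.

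Patients withdrawn for medical reasons are plausibly not a random sample with respect to outcome, and their number may differ by arm, since phototherapy has its own adverse events. The person who decides may also know the allocation, because only the EASI and vIGA-AD assessor is blinded. Reporting dropouts with their reasons, a listed secondary outcome, would show an imbalance but would not restore missing values. The drop-out allowance in the sample size protects power, not against bias. No later analysis plan can recover EASI values or SAEs that were never collected.

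**Working it through.** **The plan's own figures.** Inputs from the sample size section: 50% v 30%, two-sided 5%, 90% power, pooled Z-test, 15% drop-out.

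- The pooled formula gives 124 per arm without continuity correction and 134 with it, which matches the stated 134.
- 2 × 134 = 268, and 268 / 0.85 = 315.3, rounded up to 316, which matches. Per arm: 316 / 2 = 158.

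**Assumptions.** The article gives no rate of investigator withdrawal and does not say how such patients enter the analysis. Base case: 0 to 2% per arm before month 3 (2% of 158 = 3.2 patients). Upper bound: 5% (7.9 patients), a third of the 15% allowance. True EASI50 rates are taken as 50% and 30%, a difference of 20.0 points. Let w be the share withdrawn in an arm and f the share of those who would have responded.

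**(A) Observed cases, f = 0.** Difference = 0.50/(1 − w_NB) − 0.30/(1 − w_OTT).

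| w_NB | w_OTT | Result (points) |
|---|---|---|
| 2% | 2% | 51.02 − 30.61 = 20.4 |
| 2% | 0 | 51.02 − 30.00 = 21.0 |
| 0 | 2% | 50.00 − 30.61 = 19.4 |
| 5% | 5% | 52.63 − 31.58 = 21.1 |
| 5% | 0 | 52.63 − 30.00 = 22.6 |
| 0 | 5% | 50.00 − 31.58 = 18.4 |

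**(B) Withdrawn patients counted as non-responders.** Difference = (0.50 − w_NB × f) − (0.30 − w_OTT × f).

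- f = 0: 20.0 points whatever w is, so no bias.
- f = 0.5, 2% in one arm only: 19.0 (NB-UVB + OTT) or 21.0 (OTT).
- f = 0.5, 5% in one arm only: 17.5 or 22.5.

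**Scale.** The 95% confidence half-width at 134 per arm is 1.96 × √((0.25 + 0.21)/134) = 11.5 points. The largest base-case shift, 1.0 point, is under a tenth of that.

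**Power** (pooled Z, no continuity correction). It is 92.1% at 134 per arm. With 1%, 2%, 3% or 5% lost on top of the 15%, it is 91.9%, 91.5%, 91.2% or 90.5%.

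**Safety follow-up.** Withdrawal just after week 4 loses about 11 of 12 months of new-SAE reporting; withdrawal after month 3 loses 9. Three early withdrawals in one arm lose 3 × 11 = 33 of 158 × 12 = 1,896 planned patient-months, or 1.7%.

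**Reach of a change made at publication** (16 July 2024), assuming even recruitment from 22 February 2023 to 1 July 2024 (495 days):

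- Month 3 still ahead: recruited after 16 April 2024, 76/495 = 15.4%, about 49 of 316.
- Month 12 still ahead: recruited after 16 July 2023, 351/495 = 70.9%, about 224 of 316.

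**The case against.** The strongest reply is that the power is permissive, limited to urgent medical reasons, and sits beside a route that already keeps the data. An investigator who only needs to stop NB-UVB can stop treatment, and the retention rule then applies. Nothing in the article shows that the power would be used where stopping treatment is enough. Severe flares have a remedy within the study: "in case of severe uncontrolled AE during the study that requires rescue medication, a short course of oral prednisone can be prescribed". Sunburn has one too. This is fair and is why few patients should be affected. The wording still allows the needless loss.

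A second reply is that an extra visit with blinded examination takes place at a therapy stop, and visits may move by up to a month. A stop shortly before month 3 could therefore yield a usable EASI. This also stands, but it does not replace later assessments, nor the month-3 value after an early stop.

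A third is that a condensed article leaves operational detail to the full protocol. That holds for how contact is arranged. The rule at issue, however, is stated in the article.

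A reader might also infer that SAE reporting ends when a patient merely stops treatment. The text does not support this. The phrase on premature discontinuation stands among the conditions that define when the study ends for the patient, beside completion of all six visits and early termination of the trial. In context it means leaving the study, and treatment stoppers are encouraged to remain in it.

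Finally, the consent form asks participants "if they agree to the usage of their data should they choose to withdraw from the trial". That concerns use of data after the patient's own choice to leave, not further collection after an investigator's decision.

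**Conclusion.** The point holds as a minor one. The article lets an investigator end study participation for urgent medical reasons and provides no scheduled EASI assessment or new SAE reporting after that decision. Every figure for the effect rests on an assumed withdrawal rate. In the base case the observed-case difference lies between 19.4 and 21.0 points against a true 20.0. The wider results, 17.5 to 22.6, need 5% withdrawn in one arm only, plus an assumed response rate among those patients. If they are counted as non-responders and truly are, EASI50 is not biased at all.

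A reader might infer that the primary result or the power is at risk. The documents do not support that: power remains above 90% in every case examined, and the direction of any bias is unknown. The case for change is that it costs little and fits the intention-to-treat analysis and the long-term safety aim. Any gain from a change at publication would be mainly in later EASI and SAE data.

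**What to change.** In the withdrawal section, replace the investigator's power with wording such as: *Investigators can stop the allocated treatment for urgent medical reasons; scheduled assessments and SAE/AEoSI collection continue to month 12 as far as the patient can safely take part, unless the patient withdraws consent to follow-up.* This is the only change of substance. Align the SAE follow-up section so that reporting does not end on an investigator's decision alone. Rescue options and the clinical grounds for stopping treatment stay as they are.

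Where visits are not possible, remote contact can capture SAEs, AEoSIs and patient-reported outcomes. It cannot give a blinded EASI, which needs a physical examination, so some EASI values would remain missing. Review of medical records depends on the consent given.

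Cost: an amendment notified to the ethics committee with a registry update, a note to sites, a few already scheduled visits or contacts for patients off treatment, and possibly a check of consent for patients already enrolled. The sample size of 134 per arm and 316 in total does not change.

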#### Outcomes

Outcomes and measurement instruments from the Core Outcome Set (COS) for AE clinical trials will be used [22]. The questionnaires can be found in Additional file 3.

##### Primary outcome

Percentage of patients with EASI50 (a 50% decrease in EASI) at 3 months follow up (range EASI 0-72) [23, 24].

##### Secondary outcome

Physician-reported clinical signs at 1–3–6–9–12 months:Delta EASIPercentage of patients with EASI50vIGA-AD (range 0–4) [25].Time until a 25% reduction in mean EASI is achievedType, frequency, and quantity of topical therapies usedTime to switch to systemic therapyUse, amount, and duration of rescue medicationPatient-reported symptoms at 1–3–6–9–12 months:PGA (Patient Global Assessment) (range 0–4) [26].POEM (Patient-Oriented Eczema Measure) (range 0–28) [27, 28].NRS-11 (Numeric Rating Scale) for peak itch over the past 24 h (range 0–10) [29].Patient-reported quality of life at 1–3–6–9–12 months:DLQI (Dermatology Life Quality Index) (range 0–30) [30, 31].Patient-reported disease control at 1–3–6–9–12 months:RECAP (recap of atopic eczema) (range 0–28) [32].Patient-reported satisfaction with received treatment:PsoSat (Psoriasis care Satisfaction questionnaire) (range 0–30) [33].Cost-effectiveness at 3 and 12 months:EQ-5D-5L (EuroQol 5D 5L) (range 11,111–55,555) [34].Adapted iMCQ (iMTA Medical Consumption Questionnaire) [35].Adapted iPCQ (iMTA Productivity Cost Questionnaire) [35].Percentage of patients who achieve Treatment Target goals for AE at 3 (EASI50, delta PGA ≥  − 1), 6–9–12 months (EASI ≤ 7.0, PGA ≤ 2) [36].Adverse events of special interest (AEoSIs) and serious adverse events (SAEs) at 1–3–6–9–12 monthsPercentage of therapy failures and dropouts and reasons at 1–3–6–9–12 months, categorized according to Medical Dictionary for Regulatory Activities (MedDRA).

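### The PGA part of the 3-month treatment target, a change of at least −1, does not require improvement under either sign convention

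*Protocol article*

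**What the plan says.** The Secondary outcome section of the protocol article defines a treatment-target outcome with two sets of criteria. For 3 months the text reads "Percentage of patients who achieve Treatment Target goals for AE at 3 (EASI50, delta PGA", and the threshold printed next is ≥ −1. For the later visits the criteria are "6–9–12 months (EASI ≤ 7.0, PGA ≤ 2".

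The same section gives the instrument as "PGA (Patient Global Assessment) (range 0–4". EASI50, the companion criterion at 3 months, is fixed in the Primary outcome section: "Percentage of patients with EASI50 (a 50% decrease in EASI) at 3 months follow up".

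The article does not define delta and does not restate the 3-month PGA rule elsewhere. It lists the two 3-month criteria in one bracket, separated by a comma, without saying in words that both must be met.

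**The concern.** The later target is an upper bound on PGA and stands beside an upper bound on EASI, so a lower PGA is a better state. With change taken in the usual way, as follow-up minus baseline, improvement is negative. A lower bound of −1 on that change limits how much a patient may improve and places no limit on worsening. Taking the difference the other way round does not rescue the rule, because a threshold of −1 then tolerates some worsening.

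At stake is the 3-month treatment-target percentage. If the rule were programmed as printed, that percentage would not measure what its label says, and its comparison between arms would be hard to interpret.

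**Working it through.** **Inputs.** All come from the Secondary outcome section: PGA scores 0, 1, 2, 3, 4; rule delta PGA ≥ −1; direction, lower is better (later target PGA ≤ 2). The reference is the evident intention, an improvement of at least 1 point. The rule is a definition, so there is no stated figure to reproduce.

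**Step 1: possible changes.** On a 0–4 scale the change is a whole number from −4 to +4, nine values in all. There are 5 × 5 = 25 baseline/follow-up pairs, and a change of size d arises from 5 − |d| of them. This gives:
- improved by 1: 4 pairs
- improved by 2 or more: 3 + 2 + 1 = 6 pairs
- unchanged: 5 pairs
- worse by 1: 4 pairs
- worse by 2 or more: 3 + 2 + 1 = 6 pairs

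**Step 2: apply the printed rule under both conventions, and the corrected rule.** Cells show pairs that meet the rule.

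| PGA course | Pairs | Printed rule, follow-up minus baseline | Printed rule, baseline minus follow-up | Corrected rule: follow-up minus baseline ≤ −1 |
|---|---|---|---|---|
| Improved by 2 or more | 6 | 0 | 6 | 6 |
| Improved by 1 | 4 | 4 | 4 | 4 |
| Unchanged | 5 | 5 | 5 | 0 |
| Worse by 1 | 4 | 4 | 4 | 0 |
| Worse by 2 or more | 6 | 6 | 0 | 0 |

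**Step 3: count the changes classified wrongly.**
- Follow-up minus baseline: the rule is true for {−1, 0, 1, 2, 3, 4}; the intention is {−4, −3, −2, −1}. They agree only at −1, so 8 of 9 values are wrong.
- Baseline minus follow-up: the rule is true for {−1, 0, 1, 2, 3, 4}; the intention is {1, 2, 3, 4}. The values 0 and −1 (a one-point worsening) are wrong, 2 of 9.

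These are counts of possible values and pairs, not of patients.

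**Step 4: add the EASI50 criterion.** If both criteria are required, nobody without a halved EASI is counted. Among EASI50 responders:
- Follow-up minus baseline: unchanged or worse PGA counts as success, and gains of 2 or more points count as failure.
- Baseline minus follow-up: unchanged PGA or a one-point worsening counts as success, and no improver is excluded.

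**Step 5: check the correction.** With delta as follow-up minus baseline and the bound ≤ −1, all 10 improving pairs pass and none of the 5 + 4 + 6 = 15 others does. Reversing the inequality without defining delta is not enough: under baseline minus follow-up, ≤ −1 is met by the 10 worsening pairs and by none of the improving ones.

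**The case against.** The best defence is that the intention is plain. The criterion sits beside a percentage decrease in EASI under a treatment-target label, and the minus sign was probably meant to show the direction of a change of at least one point. An analyst would be likely to notice a target that rejects large improvers. The article also says that a detailed statistical analysis plan will be completed before database lock, and that plan may have the rule right. All of this lowers the chance of harm. It does not correct the printed rule, which is a stated criterion and not an omitted detail. A text-conversion fault cannot be shown either: the inequality signs in the same line make sense, and the minus sign is set in the same way for the utility score in the economic evaluation.

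Some stronger readings are tempting but not supported:

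- **That the 3-month target as a whole counts non-responders.** This overlooks EASI50. On the joint reading, those wrongly admitted have halved their EASI and are non-responders on PGA only.
- **That the best PGA responders are certainly excluded.** This holds only for follow-up minus baseline, and delta is undefined.
- **That 8 of 9 describes the share of patients misclassified.** It weights all changes equally and ignores EASI50. Worsening by 3 or 4 points needs a baseline PGA of 0 or 1, which is unlikely in patients with EASI ≥ 7 and insufficiently controlled eczema.
- **That the comparison between arms would reverse.** Take the EASI50 rates from the Sample size section, 50% and 30%. Let q1 (NB-UVB + OTT) and q0 (OTT) be the shares of EASI50 responders who gain 2 or more PGA points; these are assumptions. The literal rates are 0.50(1 − q1) and 0.30(1 − q0), and the order reverses when q1 > 1 − 0.6(1 − q0). That means q1 above 0.40 if q0 = 0, above 0.52 if q0 = 0.20, and above 0.64 if q0 = 0.40. With equal q the direction holds and the difference shrinks by the factor 1 − q. Reversal is arithmetically possible, but it needs literal coding and a large difference between arms for which the document gives no evidence.

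**Conclusion.** The PGA component of the 3-month treatment target is wrong as written. This follows from the printed threshold, the 0–4 range and the direction implied by the later target, and it holds whichever way delta is taken. What differs between conventions is the extent: PGA gains of 2 or more points are rejected only under follow-up minus baseline, whereas an unchanged PGA is accepted under both.

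The consequence is confined to one component of one secondary outcome at one time point. The statement that only EASI50 responders are affected assumes that both criteria are required, which is the natural reading. The number of patients affected cannot be derived from the document. The primary endpoint, the separate reporting of PGA and the 6- to 12-month targets do not use this rule. Nor does the sample size, which is set for EASI50 ("Sample sizes of 134 in both arms achieve 90% power to detect a difference between the group proportions of 20 percentage points"). The point should be corrected, but it does not threaten the main conclusion of the trial.

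**What to change.** Replace the 3-month PGA criterion with: delta PGA ≤ −1, where delta is follow-up minus baseline (PGA reduced by at least 1 point from baseline), used together with EASI50. Both the definition of delta and the direction of the inequality are needed, as Step 5 shows. Use the same wording in the statistical analysis plan and the analysis code, and settle it before database lock.

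The cost is one line of text. No data collection, visit, sample size or primary analysis changes.

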#### Participant timeline

After screening and informed consent, participants will be randomized in the NB-UVB + OTT or OTT group. Study participation will entail 6 study visits. The baseline visit will take place before therapy starts. The follow-up visits are at 4 weeks, 3, 6, 9, and 12 months. Visits may be rescheduled within 1 month of the initial planning. Extra visit(s) will take place in case of therapy switch or stop. Patients in the NB-UVB + OTT group will undergo phototherapy 3 times a week for a planned period of 12 weeks from baseline, with a possible range of 8 to 16 weeks, depending on therapy response. Therapy duration will be determined in accordance to standard clinical practice. NB-UVB can be applied in the outpatient clinic or at home. Participants in both groups will apply daily OTT for a minimum of 3 months. Patients will be asked to keep all tubes of used OTT (excluding emollients) and bring them to the study visits. During the visits, data about NB-UVB and OTT will be collected. Patients will be asked for possible SAEs and AEoSIs with details such as start and stop date, intensity/severity of adverse events, probability of relation with NB-UVB + OTT or OTT, whether the allocated therapy was interrupted, and co-medications. During all visits, a physical examination by a blinded outcome assessor will take place to assess disease severity. Additionally, a set of questionnaires will be sent to the patient. The questions can be filled out on an electronic device, either at home or during the study visit in the outpatient clinic. At baseline, 3 months, and 12 months, an additional set of questionnaires regarding disease burden on productivity and medical costs will be filled out (Fig. 1). Subjects that have completed trial participation or have discontinued prematurely will be referred back to standard eczema care.

